##### Change in physical activity levels

Physical activity is measured using the Physical Activity Scale for the Elderly. This scale contains questions related to occupational, household and leisure physical activities over the previous week [27]. The overall score is between 0 and ‘400 or more’, where a higher score indicates greater physical activity.

##### Comfort

Participants rate their level of comfort with each of their selected allocated shoes at 6 months using an 11-point NRS (where 0 = extremely uncomfortable and 10 = extremely comfortable). Higher scores indicate greater shoe comfort.

#### Other measures

##### Co-interventions

Participants record their previous (past 6 months) use of medications/supplements and other co-interventions (e.g. massage, exercises, injections etc) at baseline and at 6 months follow up. They will be classified as a co-intervention user if they respond that they have used a medication/supplement at least once per week over the past 6 months, or if they report any use of another co-intervention in the last 6 months, at either timepoint, consistent with our previous footwear clinical trials [24–26].

##### Treatment adherence

Adherence to wearing study shoes is assessed at 6 months, unless otherwise indicated, using three methods:Participants rate their level of adherence to the task of wearing their study shoes for > 6 hours/day each day, on average over the previous 6 months, using an 11-point NRS (where 0 = shoes not worn at all and 10 = shoes worn completely as instructed). Higher scores indicate better adherence.Shoe wear is recorded in log-books in the fourth week of the month, as the number of hours each day that each pair of allocated shoes was worn. The hours reported for each pair of shoes will be summed each day to give a daily total and averaged over the 7 days for each month. Number and proportion of adherent (average daily shoe wear ≥6 hours) and non-adherent (average daily shoe wear < 6 hours) participants will be reported for each month, as well as for the entire 6-month intervention period.A single Yes/No question queries if participants stopped wearing their allocated shoes without recommencing wearing them during the study. Those who indicate ‘Yes’ are asked which month they stopped wearing the shoes and to provide a brief description as to why.

##### Descriptive measures

Descriptive measures, recorded at baseline, include height, weight, body mass index (BMI), age, gender, ethnicity, current employment status, level of education, presence/absence of widespread pain (measured using the 2019 revised criteria for chronic widespread pain [28]), symptom duration, comorbidities (assessed using the Self-Administered Comorbidity Questionnaire [29]), and treatment expectation (5-point Likert scale from “no effect at all” to “complete recovery”).

##### Objective foot measures

Objective foot measures, evaluated at baseline, include the Foot Posture Index (FPI [30]), Foot Mobility Magnitude [31], and navicular drop [32]. Foot plantar pressures are recorded during walking using Pedar system insoles (Novel Pedar, Munich, Germany), which are worn inside participant’s own usual shoes and their preferred pair of the two allocated shoes, in random order. Ground reaction forces are also measured while walking: (i) barefoot, (ii) in participant’s own usual shoes and (iii) their preferred pair of the allocated shoes, using two in-ground force platforms. Plantar pressure and ground reaction force data will be reported separately from the main RCT findings as a standalone biomechanics evaluation of the effect of stable supportive compared to flat flexible shoes on these measures.

##### Usual footwear characteristics

Participants bring their most frequently worn pair of shoes (within the past month) into the laboratory at baseline, and these are assessed according to a range of characteristics including shoe weight, heel height, pitch, arch support and flexibility [18]. Number and proportion of participants who currently use flat flexible shoes, stable supportive shoes or shoes of mixed features will be reported.

### Statistical analyses

Intention-to-treat will be used to compare differences between groups for the primary analyses. If more than 5% of data are missing, we will use multiple imputation for the primary analyses and complete-case data for sensitivity analyses. For the primary outcome, differences in mean change in walking hip pain will be compared between groups using a linear regression model, adjusted for baseline values. Continuous secondary outcomes will be analyzed using similar approaches to the primary outcome. We will calculate the proportion of participants that achieve an improvement in NRS hip pain on walking that meets/exceeds the MCID (≥1.8 NRS units [17]) for each group. Risk ratios and risk differences, calculated using logistic regression models, will be used to compare between-group differences in this and other binary outcomes. Poisson regression will be used to compare between-group differences in the number of participants who experience an adverse event. A sensitivity analysis will estimate effects of wearing stable supportive shoes compared to flat flexible shoes assuming full adherence, (> 6 hours per day over 6 months) using an instrumental variables approach [33]. A secondary sensitivity analysis will estimate between-group differences on the primary outcome, adjusted for the presence of chronic widespread pain and baseline values of the primary outcome. Model assumptions will be checked using standard diagnostic plots.

To explore whether the effect of stable supportive shoes on the primary outcome is moderated by either of the pre-specified moderators of baseline BMI or foot posture, interaction terms between randomized group and each potential moderator will be included in regression models for the primary outcome, for each potential effect modifier separately. The rationale for the choice of these moderators is:BMI- we hypothesise that decreases in hip pain with stable supportive shoes (relative to flat flexible shoes) will be greater in people with a higher BMI, given that people with an increased body mass have a greater vertical loading rate compared to adults of healthy weight [34], and thus have greater scope for a reduction in loading rate with stable supportive shoes.Foot posture- we hypothesise that decreases in hip pain with stable supportive shoes (relative to flat flexible) will be greater in people with a more pronated foot posture, given stable supportive shoes are designed to reduce foot pronation, and foot pronation is associated with lower limb pathology [35].

In addition, flat flexible shoes may be perceived as being less comfortable in people with more pronated feet. Hence, to explore whether the effect of stable supportive shoes on shoe comfort is moderated by foot posture, interaction terms between randomized group and foot posture index score will be included in a linear regression model for the shoe comfort outcome at 6 months. Finally, we are also collecting a range of biomechanical measures that will be used in future studies to investigate potential mechanisms of any improvements in symptoms with footwear.

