### Sample size calculations

Based on our previous data [13], we have assumed a conservative between-participant standard deviation of 2.7 NRS units and correlation between baseline and 6-month scores of 0.20 for our primary outcome of average hip pain intensity during walking. Adjusting for baseline values, and at a significance level of 0.05, we require 48 people per group to achieve 90% power to detect the between-group MCID of 1.8 (out of 10) NRS units [17] for change in hip pain intensity during walking (baseline minus follow up). Assuming 20% loss to follow up, we will recruit a total of 120 participants (60 per group).

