**Fig. 1 Fig1:**
[figure not shown]
Flow diagram of study phases

At the baseline visit, participants complete self-reported outcomes (on paper or electronically) and are then randomized to receive either i) stable supportive shoes or; ii) flat flexible shoes. Participants are advised to wear their allocated study shoes as much as possible when wearing shoes, for a minimum of 6 hours each day, for the subsequent 6 months. We are also collecting participant descriptive measures (e.g., height, weight), objective foot measures (e.g., foot posture and plantar foot pressures) and “usual” footwear characteristics at the baseline visit. At 6 months, participants complete self-reported surveys (paper or electronic) at home to assess primary and secondary outcomes.

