#### Primary outcome

##### Change in hip pain during walking

Six-month change from baseline in average overall hip pain during walking in the last week, scored on an 11-point NRS, where 0 = no pain and 10 = worst pain possible. This outcome is valid and reliable in OA [20], and is recommended for use in OA clinical trials [21].

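### The missing-data sensitivity analysis (complete case) relies on missing at random, as the imputed primary analysis does, so their agreement cannot show robustness to dropout that depends on unobserved 6-month pain

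*Protocol article*

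**What the plan says.** The primary outcome is "Six-month change from baseline in average overall hip pain during walking in the last week, scored on an 11-point NRS" (Primary outcome). It is collected at baseline and once afterwards: "At 6 months, participants complete self-reported surveys (paper or electronic) at home to assess primary and secondary outcomes" (Procedure). The secondary outcomes come from the same 6-month survey unless otherwise specified.

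Under Statistical analyses, "differences in mean change in walking hip pain will be compared between groups using a linear regression model, adjusted for baseline values". The rule for missing data applies above a threshold of 5%: "we will use multiple imputation for the primary analyses and complete-case data for sensitivity analyses". The same section names two further sensitivity analyses. One estimates the effect "assuming full adherence, (> 6 hours per day over 6 months) using an instrumental variables approach"; the other adds adjustment for chronic widespread pain. Neither concerns missing outcomes.

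The 5% trigger is expected to be met, because Sample size calculations states: "Assuming 20% loss to follow up, we will recruit a total of 120 participants".

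A separate statistical analysis plan is announced under Randomization, blinding and allocation concealment. It is not available here.

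**The concern.** A sensitivity analysis for missing data is useful when it varies the assumption on which the primary analysis depends. The primary analysis here depends on 6-month pain being missing at random. Complete-case regression adjusted for baseline depends on missing at random too. A participant who does not return the 6-month survey has no intermediate pain score and will generally lack the other 6-month outcomes as well, so imputation has little to work with that the complete-case model lacks.

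If the two analyses agree, a report could describe the primary result as robust to missing data when only one kind of assumption has been examined. The outcome is self-reported pain and up to a fifth of it may be absent, so this robustness statement matters for how far the result can inform footwear guidance.

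**Working it through.** **Inputs.** SD 2.7, baseline-to-6-month correlation 0.20, target difference 1.8, significance level 0.05 (two-sided assumed), 90% power, 48 per group analysed, 20% loss, 60 per group recruited: all from Sample size calculations. Delta values of 1, 2 and 3 NRS units are assumptions chosen to show a range.

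**Step 1: reproduce the plan's figure.** Baseline-adjusted SD = 2.7 × √(1 − 0.20²) = 2.645. The two-sample formula with 2.645 gives 46 per group (47 with the noncentral t); with the unadjusted 2.7 it gives 48. Then 48 / 0.80 = 60 per group, 120 in total. The planned size reproduces, and the planned loss is 12 of 60 per arm, well above the 5% trigger.

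**Step 2: what the two analyses assume.** When only the 6-month score is missing, the complete-case model estimates the regression of that score on group and baseline from those observed. Imputation from group and baseline fills the gaps from that same fitted regression, so refitting returns the same group coefficient apart from simulation noise. If auxiliary variables enter the imputation model, the estimates can differ and the assumption is weaker, but it is still missing at random given what was observed.

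**Step 3: illustration.** In 2,000 simulated trials with 60 per arm, about 20% missing overall and 20 imputations from group and baseline, the mean estimated benefit of stable supportive shoes was:

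| Dropout | True | Complete case | Imputation |
|---|---|---|---|
| At random, 20% in each arm | 1.80 | 1.80 | 1.80 |
| 31% in the flat flexible arm, likelier with worse pain; 10% at random in the other | 1.80 | 0.92 | 0.92 |
| Same dropout pattern, no true effect | 0 | −0.89 | −0.89 |

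The mean absolute gap between the two methods within a trial was about 0.04 NRS in all three rows. They agree equally well with and without bias. The dropout patterns are invented, so the sizes of bias are not predictions.

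**Step 4: size without simulation.** If the missing share in an arm is p and its missing scores are truly δ units worse than imputed, that arm's mean, and hence the between-group difference, moves by p × δ.

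| δ (one arm only) | Shift at p = 0.20 | Share of 1.8 |
|---|---|---|
| 1 | 0.20 × 1 = 0.2 | 11% |
| 2 | 0.20 × 2 = 0.4 | 22% |
| 3 | 0.20 × 3 = 0.6 | 33% |

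With half the planned loss (p = 0.10) the shifts halve. With δ in both arms the net shift is the difference between the two products, and it is zero when shares and deltas are equal. Worse unseen pain in the stable supportive arm means the benefit is overstated; in the flat flexible arm, understated.

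**Step 5: what that could do to a conclusion.** With 48 per group, SE = 2.645 × √(2/48) = 0.54, and the 95% half-width is 1.96 × 0.54 = 1.06. Holding that SE fixed, an observed benefit between 1.06 and 1.26 (1.06 + 0.2) would lose significance if δ = 1 in the stable supportive arm; up to 1.46 if δ = 2; up to 1.66 if δ = 3. An observed benefit of 1.8 would survive all three.

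**The case against.** The best reply is that this is a condensed article with a separate analysis plan to follow. The imputation model is not given, and a further analysis could be added without contradicting anything in the text. That stands in part. A reader might infer that the trial will have no other missing-data check, and this document cannot establish that. The article is not merely silent, however: it names the sensitivity analysis for the imputed result, and the one it names cannot do that job.

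A reader might also infer that the two analyses must coincide and that comparing them can never reveal anything. That is too strong. In another simulation, with 20% missing in each arm and dropout and pain in the flat flexible arm both driven by shoe intolerance, complete case and plain imputation each gave a benefit of 1.49 against a true 1.80. Imputation that used the intolerance marker gave 1.80. With an informative auxiliary the two can therefore separate. Even then, neither tests dependence on the unobserved score itself.

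A third tempting inference is that participants who cannot tolerate their shoes will be the ones lost. The document does not say so. The survey is completed at home, and nothing makes it conditional on wearing the shoes. Under Treatment adherence, those who stopped "are asked which month they stopped wearing the shoes and to provide a brief description as to why" at 6 months, which expects them to be followed and analysed. The earlier knee trial is reported with 81% adherent. The 20% is a planning allowance, not a forecast of informative loss.

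Finally, a delta of 3 exceeds one planning SD (2.7), so the upper end of the range is a stress test rather than an expectation.

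**Conclusion.** The point holds in a limited form. The protocol designates complete case as the sensitivity analysis for a multiply imputed result whose outcome has a single post-baseline measurement. Both are missing-at-random analyses, so their agreement would not support a claim of robustness to outcome-dependent dropout.

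The potential effect is moderate: it depends on the loss reaching the planned 20% and on missing scores in one arm differing from those imputed. It would matter most for a result near the significance boundary. Neither the occurrence nor the direction of bias can be judged from the document, and the simulated biases rest on assumed dropout mechanisms. Nothing here shows that the primary analysis itself is wrong or that the trial will be biased. It is a cheap improvement that should be made.

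**What to change.** In Statistical analyses, replace complete case as the missing-data sensitivity analysis with a prespecified delta-adjusted imputation. Starting from the primary imputation model, shift imputed 6-month walking pain by 0 to 3 NRS units in each arm separately, re-estimate the group difference with its confidence interval over that grid, and report the shift at which the conclusion changes. Keep the complete-case result as a supplement.

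The cost is a change of wording and a few lines of analysis code, with no new data, visits or participants. The downside is that the delta range has to be chosen and justified in advance, before group outcomes are seen.

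Optionally, the analysis plan could use log-book hours and adverse events reported before dropout as imputation auxiliaries. This is limited to what dropouts have actually returned, and the article does not say when log-books come back. It would make missing at random more plausible but would not replace the delta analysis.

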### Participants

Participants with chronic hip pain are recruited from the community using advertisements (print and online), social network media (e.g., Facebook), and our clinical network and volunteer database. To be eligible, participants must meet the National Institute for Health and Care Excellence working definition of peripheral joint OA [9], based on their self-reported hip symptoms. Specifically, participants must be aged ≥45 years, experience hip joint pain with activity, and report no hip joint morning stiffness of more than 30 minutes duration. Participants are also required to have hip pain that: (i) has been present for a minimum of 3 months, (ii) is experienced on most days of the previous month, and (iii) has a severity score of > 4 out of 10 on an 11-point numerical rating scale (NRS; 0 = ‘no pain’ and 10=‘worst pain possible’) during walking in the past week.

We are excluding participants if they: (i) were diagnosed by a health professional as having gluteal tendinopathy, referred hip pain from the lumbar spine, greater trochanteric pain syndrome, or femoro-acetabular impingement syndrome, in the past 12 months; (ii) had hip surgery in the previous 6 months, or if they are planning to have surgery in the subsequent 6 months; (iii) had a hip replacement on the most painful side; (iv) currently use foot orthoses, a brace (on any lower limb joint), a gait aid or have modified/customized shoes; (v) had a hip injection in the previous 3 months or if they are planning to have an injection in the subsequent 6 months; (vi) regularly use footwear styles that would limit their ability to wear the study shoes as required (e.g. thongs, high heels, work boots etc); (vii) have any other musculoskeletal condition anywhere in the body that is worse than their study hip pain; (viii) have an inflammatory or systemic joint disease (e.g. fibromyalgia, gout); (ix) have a neurological condition affecting the spine or either lower limb; (x) cannot understand written or spoken English; and (xi) have a foot size (US) that is not between 7 to 12 for women and 8 to 13 for men. If both hips are eligible, we will use the most symptomatic hip for outcome assessments.

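### The primary model adjusts only for baseline walking pain, which the plan expects to be a weak predictor; adding baseline HOOS pain is an optional, almost free gain in precision

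*Protocol article*

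**What the plan says.** The Statistical analyses section gives the primary analysis as a between-group comparison of mean change in walking hip pain "using a linear regression model, adjusted for baseline values". It then names a secondary sensitivity analysis of the same outcome, "adjusted for the presence of chronic widespread pain and baseline values of the primary outcome". The article therefore states both models and ranks them. BMI and foot posture enter separate moderator models for the primary outcome.

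The Sample size calculations section assumes a "conservative between-participant standard deviation of 2.7 NRS units" and a "correlation between baseline and 6-month scores of 0.20". Entry requires that hip pain on walking "has a severity score of > 4 out of 10" (Participants).

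Two other baselines matter here:
- The HOOS pain subscale has 10 items on hip pain in the last week and is a secondary outcome measured at baseline. Under Randomization, blinding and allocation concealment, allocation is revealed only after the baseline primary and secondary outcomes are complete.
- The "presence/absence of widespread pain" is listed under Descriptive measures. The article does not say whether it is recorded before or after allocation is revealed.

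The same randomization section describes permuted blocks, names no stratification factor, and says that the SAP will be written while the statisticians are blinded.

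**The concern.** Covariate adjustment helps a randomised comparison to the extent that the covariates predict the outcome. On the plan's own figure, the single covariate chosen predicts the 6-month score weakly. A longer measure of hip pain is collected before allocation at no extra cost and has no stated role in the model for the primary outcome. The investigators judged widespread pain worth adjusting for, but only in a secondary analysis.

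In a linear model, baseline covariates fixed in advance leave the treatment estimate unbiased and can narrow its interval. What is at stake is a possible modest gain in precision on the one primary comparison. Its validity is not in question.

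**Working it through.** **Inputs from the article.** SD 2.7; correlation 0.20; difference 1.8; "at a significance level of 0.05" (sidedness not stated, two-sided assumed); "we require 48 people per group to achieve 90% power"; 20% loss to follow-up.

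**Input not in the article.** The prognostic strength of any baseline other than walking pain. Total R² for the 6-month score is therefore assumed over a range.

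**1. Reproduce the sample size.**
- Residual SD = 2.7 × √(1 − 0.20²) = 2.7 × √0.96 = 2.645.
- n per group = 2 × [2.645 × (1.960 + 1.282) / 1.8]² = 45.4, so 46 by the normal approximation and 47 by the noncentral t.
- Without baseline adjustment, the normal approximation gives 48 and the t version 49.
- The stated 48 agrees within 2 per group. With dropout, 48 / 0.80 = 60 per group, 120 in total, as stated.

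**2. What the baseline NRS contributes.** 0.20² = 0.04, or 4% of the variance of the 6-month score. The residual SD falls by 2.0%, and n per group falls from 48 to 46.

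**3. Change scale.** The outcome is written as change. If the SDs are equal at both times (an assumption):
- Variance of change = 2 × 2.7² × (1 − 0.20) = 11.66.
- Residual variance after baseline = 2.7² × 0.96 = 7.00.
- Baseline explains (1 − 0.20) / 2 = 40% of the variance of change.

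The residual SD of 2.645 is the same on either scale, so the treatment SE does not change.

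**4. Precision and power with 48 analysed per group.** SE = 2.7 × √(1 − R²) × √(2/48). Half-width = t × SE. Power at 1.8 comes from the noncentral t. Rows 2 to 6 use two extra covariates (five parameters).

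| Model | Total R² | SE | 95% CI half-width | Power at 1.8 |
|---|---|---|---|---|
| Planned (NRS only) | 0.04 | 0.540 | 1.07 | 91.0% |
| Extended, additions explain nothing | 0.04 | 0.540 | 1.07 | 91.0% |
| Extended | 0.05 | 0.537 | 1.07 | 91.2% |
| Extended | 0.10 | 0.523 | 1.04 | 92.6% |
| Extended | 0.15 | 0.508 | 1.01 | 93.9% |
| Extended | 0.20 | 0.493 | 0.98 | 95.1% |

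**5. Downside.** If the additions explain nothing, power goes from 0.90967 to 0.90961 with one extra covariate and to 0.90955 with two. The loss is about 0.006 or 0.012 percentage points.

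**6. How much HOOS pain alone might add.** HOOS pain overlaps with NRS pain. Suppose that baseline HOOS pain, reversed so that higher means worse, correlates 0.6 with baseline NRS and r with 6-month NRS (all assumed). Then R² = (0.04 + r² − 2 × 0.20 × r × 0.6) / (1 − 0.36).
- r = 0.20: 0.032 / 0.64 = 0.05
- r = 0.25: 0.0425 / 0.64 = 0.07
- r = 0.30: 0.058 / 0.64 = 0.09

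HOOS pain by itself may therefore sit in the lower half of the range. Reaching 0.20 would need a stronger predictor than these values suggest.

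**The case against.** The strongest reply is that nothing is wrong. Linear regression adjusted for baseline is valid and unbiased, agrees with the basis of the sample size, and already gives about 91% power. No stratification factor is named, so no design factor is missing from the model. All of this stands, and it is why the point is optional. A SAP not shown here may also add covariates. The change still concerns a model that the article states, not a missing detail.

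Several stronger readings are tempting and are not supported:
- *Baseline explains 4% of the outcome.* The 4% belongs to the 6-month score. For change it is about 40% with equal SDs, although the treatment SE is the same.
- *The other baselines go unused.* This is true only of the primary model. Widespread pain, BMI and foot posture all enter other pre-specified analyses of the primary outcome.
- *Precision is being lost.* The article gives no prognostic strength for HOOS pain or widespread pain, so the gain may be nil.
- *Widespread pain belongs in the primary model now.* Only the baseline primary and secondary outcomes are stated to precede allocation. The unblinded researcher who allocates the shoes also measures descriptive characteristics. Until the timing is confirmed, its place in a sensitivity analysis is defensible.
- *The entry threshold weakens the NRS covariate.* The 0.20 comes from earlier data whose entry rules cannot be seen here, so any restriction of range may already be in it. The same selection would also narrow a correlated HOOS score.
- *Chance imbalance in widespread pain is left unaddressed.* The sensitivity analysis addresses it, and the confidence interval already allows for chance imbalance.

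**Conclusion.** The point holds as an optional gain in efficiency, of low priority. On the plan's planning value, the only covariate in the primary model does little for precision, and a measure of hip pain known to precede allocation is available to add. For an assumed total R² of 0.05 to 0.20, the half-width narrows by between less than 0.01 and 0.09 NRS units, and power at 1.8 gains between about 0.3 and 4 percentage points. The cost if the additions are useless is under 0.02 percentage points.

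These figures rest on 48 analysed per group, SD 2.7, a two-sided 5% test, and R² values that the article does not supply. If the true baseline correlation is above 0.20, the planned model already does better than shown.

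**What to change.** Before unblinding, pre-specify in the SAP:
1. Primary model: 6-month change in walking hip pain on group, baseline NRS pain and baseline HOOS pain.
2. Add chronic widespread pain (yes/no) only if trial records confirm that it is recorded before allocation is revealed. Otherwise leave it in the sensitivity analysis.
3. If multiple imputation is triggered, include the same covariates in the imputation model.
4. Keep the model adjusted only for baseline NRS as a sensitivity analysis.

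The cost is a few lines in the SAP and one or two degrees of freedom. No new data are needed, and the sample size is unaffected.
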